## Abstract

**Background:**

Adolescents in low- and middle-income countries face significant nutritional challenges, including undernutrition, micronutrient deficiencies, poor dietary habits, and food insecurity. These issues adversely affect their growth, development, and long-term health. Despite their vulnerability, adolescents are frequently excluded from nutritional program planning due to limited data, weak intervention delivery platforms, and underdeveloped policies.

**Methods/design:**

The Nutrition and Adolescence in Rural Nigeria (NARN’ia) study aims to address this gap through a comprehensive assessment of energy requirements in adolescent girls (N = 70; ages 10–19 years) in Nigeria. NARN’ia will combine multiple methods: 24-hour dietary recall using the (INDDEX24 app); physical activity monitoring via accelerometry; anthropometric assessments of body composition, and the doubly labeled water method to measure total daily energy expenditure and body composition.

**Discussion:**

Findings from this study will inform evidence-based nutritional guidelines tailored to adolescent girls in Nigeria. By integrating robust methodologies, NARN’ia will contribute foundational data on adolescent energy needs, supporting future research and policy development in Nigeria and other low- and middle-income countries.

**Trial registration:**

ClinicalTrials.gov NCT06601959

## 1. Introduction

Adolescence is a transitionary developmental phase between childhood and adulthood that is characterized by changes in body composition such as changes in the ratio of fat to fat-free mass, increase in skeletal mass, as well as changes in primary and secondary sexual characteristics [1,2]. Adolescence offers a second opportunity for rapid growth and development, and the final window to eradicate stunting [3]. During this period, humans gain up to 50% of their adult weight, more than 20% of their adult height, and 50% of their adult skeletal mass [4]. These growth and maturational processes lead to elevated daily energy requirements during adolescence and require a corresponding increase in nutritional intake [5], however these requirements are not always met.

A critical element in formulating health and nutrition policies for adolescents is a clear understanding of their energy requirements and dietary intake [6]. Energy requirements refer to the amount of food energy necessary to balance total energy expenditure (TEE), supporting physical activity as well as growth and development [7]; Torun, 2005). In the past, these analyses relied heavily on survey-based estimates of TEE, daily physical activity, and diet [8]. However, in recent decades, the development of accelerometry to objectively measure daily physical activity, and the doubly labeled water (DLW) method to objectively measure TEE during normal daily life have improved assessments of these key variables, and instruments for recording dietary intake have improved [5,9–12].

### 1.1. Dietary assessment

Dietary assessment involves measuring food intake, dietary diversity, and feeding behaviors of individuals, groups, or populations. It includes comparing these factors to recommended dietary guidelines and tracking changes in dietary habits over time [13–15]. Self-reported dietary surveys ask participants to detail all food and drink consumed, including portion sizes, locations, and times of consumption [16]. This information is often collected using dietary assessment software linked to food composition databases, which convert reported foods and beverages into energy and nutrient values [17].

The 24-hour dietary recall is a dietary assessment tool in which participants are asked to recall and describe all foods and beverages consumed within the past 24 hours, usually of the previous day. A trained interviewer typically conducts the recall however, the process can also be self-administered using a mobile application. To enhance the accuracy of the recall, the multiple pass method is used. This involves participants providing information on all their consumptions with increasing details such as the variety of produce, preparation methods, and added ingredients over multiple passes [18]. The 24-hour dietary recall method can also be employed to assess dietary diversity and nutritional quality by determining the number of different food groups consumed.

The accuracy of these methods is contingent on several key factors such as participant compliance, i.e., their willingness and ability to accurately describe their food and beverage consumptions [17]; interviewers’ ability to ask the necessary questions and accurately interpret and record participants’ responses; and the accuracy of the food composition database used to convey the reported intakes into energy and nutrient measurements [17,19,20]. Errors in dietary recall can be mitigated through thorough training of both participants and interviewers, along with the use of a reliable food composition database. This multifaceted approach ensures that the dietary data collected accurately reflects the participants’ consumptions.

### 1.2. Physical activity assessment

Our current understanding of physical activity levels among adolescents remains limited by the precision of assessment methods, and the difficulties inherent in measuring habitual physical activity in this demographic [21,22]. These limitations hinder comprehensive insights into the impact of physical activity on adolescent health and development. Low physical activity during adolescence has been associated with increased risk of obesity, cardiovascular diseases, and diabetes [23–25]. Over 80% of adolescents worldwide fail to meet the current recommendations of at least one hour of daily physical activity [4,26–28].

A prior study conducted in Nigeria utilizing activity diaries kept by participants to measure energy expenditure revealed that energy expenditure was low among adolescents with notably higher levels among boys compared to girls across all ages [2]. However, the accuracy of diaries in capturing the patterns of physical activity remains uncertain, underscoring the need for additional research that more comprehensively assesses both the intensity and duration of physical activity over an extended period.

Activity monitoring using accelerometry has been validated for measuring energy cost in children and adolescents [29]. Triaxial accelerometers detect the magnitude and direction of acceleration across all three planes of motion simultaneously [30]. This method is widely used in large-scale studies to assess and quantify human movement and activity patterns [31]. Despite its global popularity, its application in Nigeria has been limited, with only one study identified that employed this technology [32] and none specifically in the population under investigation here. Therefore, this study has the potential to offer unique insights into energy expenditure research in Nigeria and globally, potentially filling crucial gaps in understanding physical activity patterns and their impact on health outcomes in this demographic.

### 1.3. Body composition

Body composition refers to the proportions of fat, muscle, bone, and other tissues that make up an individual’s body mass (BM). The primary components of body composition are fat mass (FM), which includes all fat tissue in the body, and fat free mass (FFM) including muscle, bone, organs, and water [33]. Maintaining a healthy body composition is important for overall health, physical performance, and disease prevention which are influenced by diet, physical activity levels, genetics, and age [34].

Body composition studies are crucial for informing strategic interventions and policies aimed at meeting nutritional needs. However, data on body composition among adolescents, particularly in rural and low to middle-income countries (LMICs), has relied on techniques like anthropometric measurements, e.g., skinfold thickness (SFT), and total body electrical conductivity [35,36]. Anthropometry is a rapid and cost-effective technique for assessing body composition [37], but it is limited in its ability to accurately assess body composition [38,39]. There remains a critical gap in foundational data for adolescents who are experiencing dynamic changes in nutritional needs and metabolism [5].

The use of isotope dilution to measure total body water (TBW) has become one of the main methods for conducting body composition analysis [36,40]. In a model of body composition that includes FM and FFM, water is a crucial component of FFM [41] and because the hydration of FFM remains relatively constant among healthy individuals [42], FFM can be calculated from TBW measurement with deuterium dilution [43]. Since deuterium is one of the isotopes used in DLW assessments of energy expenditure, deuterium dilution assessment of TBW and FFM is a standard output for DLW analyses.

### 1.4. Energy expenditure

The DLW method is also considered the gold standard for estimating TEE under free-living conditions with minimum interference to daily life [5,36,40,44–48]. This technique quantifies the production rate of carbon dioxide (CO_2_) by measuring the differential elimination rates of deuterium (^2^H) and oxygen-18 (^18^O) from the body’s total water pool. Participants drink a dose of water (1.25 grams per kg body weight) that is enriched to 6% ^2^H_2_-O and 10%H_2_-^18^O. Deuterium (^2^H) is eliminated through water in bodily fluids (e.g., urine, expired water vapor, sweat), whereas oxygen-18 (^18^O) exits through both bodily fluids and carbon dioxide (C-^18^O_2_) [49]. The difference in the elimination rates of these isotopes can therefore be used to calculate the rate of CO_2_ production. Carbon dioxide (CO_2_) is a waste product of energy metabolism, and therefore the rate of CO_2_ production can be used to calculate the rate of energy expenditure.

DLW has demonstrated high accuracy in calculating TEE [50–52]. Despite its efficacy, DLW usage is predominantly observed in high-income countries (HICs) [7, 53] largely due to associated prohibitive costs and limited analytical expertise [54, 55]. Similarly, to other LMICs, the use of DLW in Nigeria is limited [56–58] and this forthcoming study focusing on adolescents will be the first of its kind in the region.

The Nutrition and Adolescence in Rural Nigeria (NARN’ia) study will integrate the DLW method with dietary assessments using the 24-hour INDEXX App, anthropometric evaluations of body composition, and accelerometry for physical activity quantification. Together, these methods will provide evidence-based data essential for designing and implementing nutritional programs tailored to the needs of adolescent girls in the region. Furthermore, this research initiative aims to establish a foundational framework for future studies on energy requirements in Nigeria and other LMICs.

### 1.5. Nutritional challenges in Nigeria

There are approximately 600 million adolescent girls (aged 10–19) worldwide, with nearly 90% residing in developing nations [59]. In Nigeria alone, the number exceeds 25 million, representing about 13% of the total population [60,61]. Adolescents worldwide face numerous nutritional challenges that impact their growth, development, and future health. Undernutrition, micronutrient deficiencies, poor dietary practices, and food insecurity are prevalent in low and middle-income countries (LMICs). Increasingly, these issues coexist with rising obesity rates in LMICs, a phenomenon known as the dual burden of malnutrition [62].

A considerable number of adolescent girls across Africa suffer from chronic malnutrition, severely affecting their health and development. In Nigeria specifically, about 1 in 4 adolescent girls (ages 15–19) are malnourished, and 61% are anemic [63]. Despite these alarming statistics, in Nigeria, similarly to most developing countries, nutrition initiatives have primarily focused on young children and/or adult women, leaving this demographic quite neglected [64]. This neglect is concerning because adolescent girls are particularly vulnerable to malnutrition due to their increased need for nutrients, cultural influences that affect their eating habits, and susceptibility to environmental influences prevalent in impoverished regions [65,66]. Addressing their nutritional needs is a crucial step toward breaking the cycle of intergenerational malnutrition, chronic diseases, and poverty [67]. However, solving these challenges and improving adolescent girl nutrition requires accurate and reliable measures of daily energy needs.

NARN’ia aims to conduct the most comprehensive assessment of energy requirements in adolescent girls in Nigeria to date. This study will integrate dietary assessments using the 24-hour recall method; physical activity levels using accelerometry; anthropometric evaluations of body composition, and the DLW method for assessing both body composition as well as indirect calorimetry. Together, these methods will provide evidence-based data essential for formulating appropriate nutritional guidelines to support healthy growth and development of adolescent girls in Nigeria. Furthermore, this research initiative will establish a foundational framework for future studies on energy requirements in Nigeria and other LMICs.

## 2. Methods and project design

### 2.1. Trial registrations and ethical clearances

The study protocol was approved by the Institutional Review Board of the Duke University Health System (Durham, NC, USA; protocol 00114378). The University of Nigeria Teaching Hospital Health Research Ethics Committee (NHREC/o5/01/2008B-FWA00002458–1RB00002323) provided ethical clearance ensuring that the research plan complies with international ethical standards for human subject research. The study was also approved by the Abia State Secondary Education Board. The ClinicalTrials.gov identifier is NCT06601959.

### 2.2. Study participants

The NARN’ia study is being conducted in Ikwuano Local Government Area of Abia State, located in southeast Nigeria. Ikwuano is a rural region primarily inhabited by crop farmers and traders from the Igbo ethnic group. The recruitment goal for the NARN’ia study is a total of 70 adolescent girls selected from four secondary schools in Ikwuano. The schools were selected in consultation with local education authorities based on geographic spread, accessibility, school size, and willingness to participate. Within each selected school, eligible participants are identified. From this pool, students are randomly selected through balloting without replacement.

Inclusion criteria include female students between the ages of 10 and 19 years who provide verbal assent and have written parental consent. Exclusion criteria include students with physical disabilities, those who are ill during the study period, and students attending boarding schools due to their more restricted living conditions.

Due to logistical constraints particularly the delayed and phased delivery of research materials from Duke University to the study site at MOUAU, the study is being conducted in two phases. This phased approach also allows the local team to manage recruitment and data collection more effectively. Importantly, both phases follow the same recruitment procedures, inclusion and exclusion criteria, and data collection methodology to ensure consistency and comparability of results.

In Phase 1, which took place in early 2024, 40 participants were recruited from four secondary schools. In Phase 2, an additional 20 participants are being recruited beginning in early 2025. In both phases, the same types of data are collected, including anthropometric measurements (height, weight, body composition), assessments of physical activity levels, and 24-hour dietary recalls. There are also no methodological differences between the two phases.

The study team has also considered the potential influence of seasonal factors, such as school holidays and variations in food availability and physical activity patterns, particularly between the dry and rainy seasons in Nigeria. While both phases are scheduled to occur during the school term to ensure access to participants and minimize variability due to holidays, possible seasonal differences in food consumption and activity patterns will be documented and statistically accounted for in the final analysis.

Students were informed about the study, and those interested in participating provided written assent in the presence of their teachers and school administrators. Prior to final recruitment, meetings were held with parents of students who assented and with school officials. During these sessions parents and students were informed about the study’s purpose, eligibility criteria, procedures, and equipment. Final enrollment occurred after written parental consent was received. All communications were conducted in English or Igbo, based on participants’ preference.

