### 2.3. Sample size

The sample size for the NARN’ia study was informed by similar studies using doubly labeled water (DLW) and accelerometry to assess energy expenditure and physical activity in adolescents, particularly in low- and middle-income countries [55,68–70]. Studies in comparable populations have used sample sizes ranging from 21 to 60 participants. Given the complexity and high cost of DLW analysis and the logistical challenges of conducting field-based research in rural Nigeria, we selected a target recruitment sample size of n = 70 as both practical and methodologically robust. Power analyses conducted using G*Power software (version 3.1) indicate that a sample size of 70 achieves approximately 70–91% power to detect medium effects in multiple linear regression models at a significance level of α = 0.05 when testing between 2–4 predictors [71]. This sample size is expected to be sufficient to detect meaningful associations between total energy expenditure and key variables such as body composition, physical activity, dietary intake, and age etc., while balancing the practical constraints of cost and logistics of conducting research in rural Nigeria with scientific rigor.

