## 5. Trial status

Data collection for Phase 1 of this study was completed in May 2024, and preliminary data analysis is currently underway. Recruitment for Phase 2 has been completed, and data collection is actively ongoing. The study remains on track for final analysis and dissemination following the completion of both phases.

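### The two recruitment phases add up to 60 girls, but the abstract, the recruitment goal and the power statement all rest on 70; if 60 is the true number, the stated power does not apply

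*Protocol article*

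**What the plan says.** Three places give 70 girls:

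- The abstract (Methods/design) describes the sample as "adolescent girls (N = 70; ages 10–19 years").
- Section 2.2 says that the recruitment goal "is a total of 70 adolescent girls selected from four secondary schools in Ikwuano".
- Section 2.3 says "we selected a target recruitment sample size of n = 70 as both practical and methodologically robust". It then gives power of roughly 70% to 91% at that size, for medium effects in multiple linear regression with 2 to 4 predictors and α = 0.05.

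The phase counts, also in section 2.2, give a different total. The section says that "the study is being conducted in two phases". For the first it reports: "In Phase 1, which took place in early 2024, 40 participants were recruited from four secondary schools". For the second: "In Phase 2, an additional 20 participants are being recruited beginning in early 2025".

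Section 5 adds: "Recruitment for Phase 2 has been completed, and data collection is actively ongoing". It gives no final count for Phase 2. The article describes no third phase, no top-up and no lowered target.

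**The concern.** The goal and the phase counts stand in the same section and differ by 10 girls. Because Phase 2 recruitment is reported as closed, the gap cannot be read as recruitment still to come.

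The sample size is a headline design figure, and the power statement in section 2.3 is computed from it. A reader cannot tell whether 60 or 70 girls were enrolled, nor whether the quoted power describes the study being run. If the number is 60, the article claims more power for its regression models than the design gives.

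**Working it through.** **Count.** Phase 1 is 40 and Phase 2 is 20 (both section 2.2). 40 + 20 = 60, and 70 − 60 = 10, which is 10/70 = 14% of the target.

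**Inputs for power.**

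- From section 2.3: N = 70, α = 0.05, u = 2 to 4 predictors tested, a medium effect, stated power of about 70% to 91%.
- Assumed: f² = 0.15, the conventional medium value, because the article gives no number; values from 0.13 to 0.20 are also shown.
- Assumed: the overall F test of the regression, because the article does not name the test.

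**Formula.** Power = P(F′ > F_crit), where F′ is noncentral F with u and N − u − 1 degrees of freedom and noncentrality λ = f² × N, and F_crit is the 95th percentile of the central F.

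**Step 1: reproduce the stated range at N = 70.** λ = 0.15 × 70 = 10.5.

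| Predictors | df | Power |
|---|---|---|
| 2 | 2, 67 | 81.7% |
| 3 | 3, 66 | 75.6% |
| 4 | 4, 65 | 70.4% |

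The lower end (70%) reproduces with 4 predictors, which supports f² = 0.15 as the value used. The upper end (91%) does not: the overall test peaks at 82%, and with 2 predictors it would need N = 91 to reach 91%. The nearest match at N = 70 is a two-sided test of a single coefficient, at 89.1%.

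**Step 2: the same calculation at N = 60.** λ = 0.15 × 60 = 9.0.

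| Predictors | df | Power | Change from N = 70 |
|---|---|---|---|
| 2 | 2, 57 | 74.7% | −7.0 points |
| 3 | 3, 56 | 67.7% | −7.9 points |
| 4 | 4, 55 | 62.1% | −8.3 points |

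The 3- and 4-predictor cases fall below 70%. The 2-predictor case stays inside the stated band.

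**Step 3: how far the result depends on the assumptions.** Overall test with 4 predictors:

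| f² | N = 70 | N = 60 |
|---|---|---|
| 0.13 | 63% | 55% |
| 0.15 | 70% | 62% |
| 0.18 | 79% | 71% |
| 0.20 | 84% | 76% |

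A two-sided single-coefficient test at f² = 0.15 falls from 89% at N = 70 to 84% at N = 60.

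If f² is instead set so that the overall test with 2 predictors gives 91% at N = 70 (f² about 0.196), N = 60 gives 86%, 80% and 75% for 2, 3 and 4 predictors. That value no longer fits the stated 70% floor, because 4 predictors at N = 70 then give 83%.

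Power is lower at 60 than at 70 under every setting tried.

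**The case against.** **60 may not be the true number.** Three places say 70, and only the Phase 2 figure of 20 leads to 60. Section 2.2 words it as recruitment in progress, and section 5 closes recruitment without giving a count, so 20 could be a slip for 30. This stands. A reader might infer that the study has certainly lost its stated power, but the article does not establish that. It establishes that its own numbers conflict, and the loss of power is conditional on 60.

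**The size of the loss rests on choices the article does not make.** It names neither f² nor the test, and the overall F test at f² = 0.15 does not reach the stated 91% even at 70. This also stands. A reader might infer from the N = 60 table that no analysis reaches 80% with 60 girls. That is true only of the overall test at f² = 0.15; the single-coefficient test gives 84%, and larger values of f² also pass 80% in some cases. Section 2.3 does not claim 80% either; its own floor is 70%.

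**The consequence is modest.** The study's stated aim is to assess energy requirements, and no primary hypothesis test is named. Section 2.3 also justifies the size by cost, logistics and comparable studies of 21 to 60 participants, a range that 60 still meets. This limits the harm but does not remove the contradiction, because the power statement is printed for a number that the phase counts do not support.

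**Allowance for unusable samples or dropout.** A reader might want to add that none is shown. A condensed article commonly leaves that to the full protocol or analysis plan, so it forms no part of this point.

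**Conclusion.** The contradiction is plain in the text and needs correcting: 40 + 20 = 60 against 70 in the abstract, section 2.2 and section 2.3, with 10 girls (14%) unaccounted for and Phase 2 recruitment reported as complete.

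If 60 is the true number, the power stated for 70 does not apply. With f² = 0.15 and the overall F test, both assumed, the loss is 7 to 8 points, and the 3- and 4-predictor cases drop below the stated floor. Other choices of effect size or test change the size of the loss but not its direction.

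Correcting the number alone would not restore the stated upper end, since under these assumptions 91% is not reached at 70 either.

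**What to change.** 1. Reconcile the phase counts with the total, and give the one true number in the abstract, section 2.2 and section 2.3.
2. Re-run the power calculation for that number and restate it, naming the effect size as a value, the test, and the number of predictors tested. At 60 girls, with f² = 0.15 and the overall F test, the statement would read about 62% to 75% for 4 down to 2 predictors. If the sponsor used a different test or effect size, those should be named and the matching figures given.
3. If 70 girls were in fact recruited, correct the phase counts in section 2.2 instead. The upper end of the power range should still be checked and its basis stated.

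The cost is a few changes of wording and one re-run of the power calculation. No extra enrolment is needed. The only price is that the stated power may become less favourable.
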